## Abstract

**Background:**

By changing the paradigm of neonatal intensive care and integrating parents into the care team, the ‘family integrated care’ (FICare) model developed in Canada ensures that infants receive more consistent care and parents are better able to care for their infants within the neonatal intensive care unit (NICU) and at home. However, Chinese health policy dictates that parents are not allowed into the NICU during their infant’s stay, which inhibits this type of parent–infant interaction and may affect infant outcomes. This project aims to demonstrate that allowing parents to care for their newborn infants in the NICU improves the medical outcomes of infants.

**Methods/Design:**

This cluster randomized controlled trial will evaluate the feasibility and efficacy of FICare in six Chinese tertiary-level NICUs in China – three ‘intervention’ and three ‘control’ NICUs. The study steps are: (1) planning and preparation; (2) staff recruitment and training; (3) pilot study in two centers; (4) interim analysis and confirmation of sample size for main study; (5) implementation of main study; (6) data analysis and preparation and publication of study reports. The primary outcome measure is duration of hospital stay from admission to discharge. Secondary outcome measures are: (1) clinical outcomes, such as nosocomial infection, (2) weight gain, (3) breastfeeding, (4) time to full feed, and (5) maternal stress.

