### Setting and sample

In this multicenter cluster randomized control trial, six tertiary-level NICUs in three different cities (two NICUs in each city) will be randomized to two groups: FICare or control groups, such that the three NICUs in each group are from different cities. A total of 588 eligible infants (294 in each group, and 98 in each NICU) for whom parental consent has been obtained will be enrolled (the enrollment rate will be approximately 11 to 18 %). An internal pilot study will be first conducted in two NICUs, one from the FICare group and one from the control group. In all, 90 infants (45 from each NICU) will be recruited for the pilot study. The recruitment period of the pilot study will take around 10 months. It is estimated that 540 to 640 eligible infants (the estimated enrollment rate is approximately 21 to 25 %) are admitted to attending NICUs each year.

Patient inclusion criteria are:Infants are born at a gestational age of more than 28 weeks but less than 35 weeks;Infants have been receiving enteral feeds for more than 24 h; andInfants have vital signs that have been stable for more than 24 h. Patients must meet all three criteria.

Patient exclusion criteria are:Infant requires either invasive or non-invasive ventilation support;Infant requires surgical intervention;Infant is receiving palliative care;Parents have severe social issues or there is a language barrier;Infant is likely to be discharged within 1 week;Care-provider is not willing to commit to staying in the hospital for more than 6 h per day;Parents refuse to give consent; orInfant weighs less than 400 g at birth.

Patients, parents or care-givers meeting any one of these criteria should be excluded.

Patient discharge criteria are:Daily enteral feed is more than 160 ml/(kg day) and infants tolerate enteral feeding well;The infant has regained birth weight plus the body weight is more than 2 kg;Vital signs are stable;Neither intravenous medication nor oxygenation is needed;The baby gains weight for at least three consecutive days; andA car-seat test is passed if the parents drive.

Patients must meet all six criteria before being discharged home.

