The primary outcome measure is the total hospitalization period. The secondary outcome measures are: total medical expenses, infection incidence per 1000 hospitalization days, rate of breastfeeding, parental confidence and stress, assessment of feasibility and necessity of model of care, development of guidelines for supervising parents participating in the FICare model in the NICU.

The key independent variables are: rate of breast feeding, weight gain and growth speed, infection incidence per 1000 hospitalization days, total hospitalization period. The extra expenses for medical staff will include: salary for the hired research nurse, stipend for engaging doctors and nurses for extra hours of work related to the study (compared with the control groups), expenses for preparing parent education materials.

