### Data analysis

Data analysis will be conducted on an intention-to-treat basis. To take into account the clustering effect, Student’s *t* test adjusted for the inflation factor (or design effect) [11, 12] will be used, to compare the primary outcome between the FICare and control groups. Furthermore, a two-level hierarchical linear regression model will be used to compare the primary outcome measure between the two groups, accounting for patient-level characteristics, such as gestational age, small for gestational age, sex, Apgar score at 5 min, maternal age, delivery mode, maternal hypertension, chorioamnionitis, maternal education, and the NICU-level covariates (NICU size, number of nurses, and neonatologists). To take into account the cluster effect, a symmetric covariance matrix structure will be used for the models.

The secondary outcome measures will also be compared between the two groups using Student’s *t* test for continuous variables and the chi-square test for categorical variables adjusted for the inflation factor. A two-level hierarchical linear regression model or a logistic regression model, as appropriate, will be applied for the comparison of the outcomes between two groups, accounting for patient-level and NICU-level characteristics.

To assess the rate of growth for the two groups, we will further examine the rate of weight change over time, if applicable. Linear or nonlinear mixed-effect models for longitudinal data will be used to compare the rate of change in weight gain between the two groups, adjusted for duration of hospital stay, and patient-level and NICU-level characteristics. An interim analysis for the internal pilot study will first be conducted using similar methods, if applicable. The preliminary results will then be used to re-justify the sample size, using the method of Lake et al. [10].

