### Ethical approval and trial registration

The study received ethical approval from the ethics committee of the Third Xiangya Hospital of Central South University for Clinical Research. The ethical approval number is (2013) Ethic_CSU(S123). The study has been registered in Chinese Clinical Trial Registry (registration number, ChiCTR-TRC-14004736). Informed consent has been obtained from each participant.

In addition, the following procedures were taken to ensure compliance with ethical standards:To obtain informed consent from each participating parent before enrollment;To set up a system for incidence reporting, including the use of time limitations (less than 24 h) and the need for a formal written report;To use patient numbers instead of patient names when summarizing data;To obtain parents’ written approval for publishing their names or pictures on the research update;To respect parents’ decisions to join or leave the study at any time.

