China is a large country with 30 provinces, each with varying economic status, a factor that may have a significant influence on the outcomes of infants in the NICU. In addition, we do not want to conduct this study in a NICU with too many beds, as it may be difficult to maintain the quality of the study in a larger NICU, particularly in terms of problems with human resources, such as varying availability of nurses or inconsistent shift patterns. Our main objective during our baseline research was to collect data on Chinese NICUs, including the number of NICU beds, mean birth weight of patients, percentage of preterm babies, percentage of babies with gestational age <32 weeks, nurse–patient ratio, mean hospitalization period, total medical expense per patient, top three reasons for early discharge home, re-admission rate within 30 days after discharge, and possibility of allowing parents to enter NICU (0 = impossible, 1 = probable, 2 = very possible, 3 = already allowed). As a result of our analysis we identified and recruited six NICUs at the same academic level from three provinces, all from cities with an above-average economic level. The NICUs are all similar in size and have a similar patient mix. Thus, we have tried to ensure that program implementation will be as consistent as possible across the six sites with fewer barriers linked to economic status and availability of hospital and parent resources. Following success in this study we will be able to expand the program to examine whether it is feasible in regions with a lower economic status and more financial challenges.

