We estimate that there will be a drop-out rate of approximately 10 % of families who enroll in the study, mostly owing to financial issues or time constraints. To minimize the effect of the biases this could introduce, we will conduct analysis with an intention-to-treat basis. There are limitations to this study. Unlike a randomized controlled trial, where patients are randomized rather than centers, some potential confounders, such as sex, gestational age, or birth weight, cannot be complete controlled for. To minimize the biases that may exist between two centers because of this, we will use multilevel models to compare the outcomes between two groups adjusting for these potential confounders in the analysis stage. We will also adjust the analysis for any potential confounders due to differences in the NICUs (NICU size, number of nurses, and neonatologists). Since the eligible infants in a NICU cannot be identified before randomization, i.e., consent cannot be obtained before randomization, this could introduce a selection bias. To minimize this bias, we will ensure that the recruitment of infants is conducted by a research coordinator who is blind to group allocation.

The project proposed here will take the principles of the FICare model as described by the Mount Sinai Hospital group and see how they can be applied to Chinese NICUs and what the outcomes are. The key pillars of this project are [8]:Mothers or close family members are present in the NICU to take care of their newborn infants and collaborate with the NICU medical team in the infant’s care;Parent education is provided, such that parents can truly participate;Infant holding and parents being present at their infant’s bedside is supported by unit policies, physical, and environmental supports;Nurses are provided with tools and education to enable families to be part of the care team; andThe entire care team supports the model of care.

The project is a multicenter cluster randomized controlled trial and is not a technology-based project. The approach used in this project could be transferable to many other areas of medical care, such as pediatrics, chronic care, and geriatrics. Data in this project can be used to inform health policy in NICUs across China so that parents can be allowed to enter the NICU and be at their infant’s bedsides during baby’s hospitalization, and modifying the design of NICUs in China to facilitate the participation of parents in caring for their newborn infants.

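### Stay is counted from admission, before individual exposure begins, while the unadjusted primary test and the named covariates leave out birth weight and acute severity; the covariate and data lists also disagree

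*Protocol article*

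**What the plan says.** **Outcome.** The abstract's Methods/Design paragraph says: "The primary outcome measure is duration of hospital stay from admission to discharge". Data collection procedures gives the same measure another name: "The primary outcome measure is the total hospitalization period".

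**Entry.** Setting and sample requires, among other things, "Infants have been receiving enteral feeds for more than 24 h" and an equally long period of stable vital signs. It excludes an infant when "Infant requires either invasive or non-invasive ventilation support" applies. Ethical approval and trial registration adds: "To obtain informed consent from each participating parent before enrollment". Under Interventions, most of the care elements are delivered by the infant's own parents.

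**Analysis.** Data analysis puts first, for the primary outcome, a t test adjusted for the design effect. A two-level linear model follows, with patient characteristics "such as gestational age, small for gestational age, sex, Apgar score at 5 min, maternal age, delivery mode", then maternal hypertension, chorioamnionitis and maternal education, plus NICU size and staffing.

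**Promise of adjustment.** The Discussion refers to "some potential confounders, such as sex, gestational age, or birth weight" that cannot be fully controlled when centres are randomized, and says the multilevel models will adjust for them.

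**Data.** The list in Data collection procedures includes birth weight, SNAPPE-II, ventilation and oxygen periods, and age at starting enteral feeds. It does not include chorioamnionitis, maternal age or maternal education.

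**The concern.** The days between admission and eligibility count in the outcome, but the infant's parents are not yet delivering FICare. Those days depend largely on how ill the infant was at first and on how the unit handles ventilation and feeding. They add variation that the individual intervention cannot reduce.

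With three NICUs per arm, randomization cannot be relied on to balance early illness. Any chance difference between arms passes in full into an unadjusted difference in total stay. The t test removes none of it. The regression removes some through gestational age, but the acute-severity score that the trial collects is not among its named terms.

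Two mismatches need no assumption. The Discussion says birth weight will be adjusted for, and Data analysis does not name it. Data analysis names three covariates that the data list does not contain. A model that cannot be fitted from the listed data invites a choice of covariates after results are seen.

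**Working it through.** **Step 1: reproduce the plan's figure.** Inputs from Sample size calculation: difference 5 days, SD 15, intra-cluster correlation 0.01, power 80%, drop-out 10%, 98 infants per hospital. Alpha is not stated; two-sided 0.05 is assumed.

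- Unclustered n per arm = 2 × [15 × (1.96 + 0.8416) / 5]² = 141.3.
- Evaluable infants per NICU = 98 × 0.9 ≈ 88; design effect = 1 + (88 − 1) × 0.01 = 1.87.
- 141.3 × 1.87 = 264.2 evaluable per arm; 264.2 / 0.9 = 293.5 enrolled per arm.

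The plan gives 293 per arm (586 in total) in that section, and 294 (588) in Setting and sample. The sample size is not at fault here.

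**Step 2: baseline standard error.** Between-NICU variance = 0.01 × 225 = 2.25; within-NICU variance = 222.75.

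- SE = √[2 × (2.25/3 + 222.75/264)] = √[2 × (0.75 + 0.84375)] = 1.785 days.
- Normal-approximation power = Φ(5/1.785 − 1.96) = 80%, matching the plan.

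**Step 3: SE if the added covariates remove part of the within-NICU variance.** The document gives no figure for this share, so a range is assumed. Between-NICU variance is held at 2.25.

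| Share removed | Within-NICU variance | SE (days) | Power, normal approx. |
|---|---|---|---|
| 0% | 222.75 | 1.79 | 80% |
| 10% | 200.48 | 1.74 | 82% |
| 20% | 178.20 | 1.69 | 84% |

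**Step 4: gain beyond covariates already named.** Suppose gestational age, small for gestational age and Apgar score already remove 20% or 40% (assumption), and the new terms remove 10-20% of what is left.

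- Start at 20%: within-NICU variance 178.20 falls to 160.38-142.56; SE 1.69 falls to 1.65-1.61.
- Start at 40%: 133.65 falls to 120.29-106.92; SE 1.59 falls to 1.55-1.52.

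The further reduction is about 0.03-0.08 day, against 0.05-0.10 day when starting from no covariates.

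**Step 5: chance imbalance in pre-eligibility days.** If these days have SD 5, 7 or 10 (assumption) and intra-cluster correlation 0.01, the 95% range of the between-arm difference in means is ±1.96 × SD × √(2 × 1.87/264), which is ±1.2, ±1.6 or ±2.3 days. This is sampling error, not bias. It shows how much of an observed difference in total stay could come from days before enrolment.

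**Step 6: set the lists side by side.**

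| Item | Data analysis (model) | Data collection list | Discussion |
|---|---|---|---|
| Birth weight | not named | listed | to be adjusted for |
| SNAPPE-II | not named | listed | not mentioned |
| Chorioamnionitis | named | not listed | not mentioned |
| Maternal age | named | not listed | not mentioned |
| Maternal education | named | not listed | not mentioned |

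**The case against.** **The covariate list is open.** It begins with such as, and a full analysis plan may settle the final set. Gestational age with small for gestational age carries much of the information in birth weight. This stands in part: the omission of birth weight is a mismatch with the Discussion, not proof that it will be left out. It does not help the t test, which comes first and has no covariates.

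**The data list may be incomplete.** Parent questionnaires are also used and could record maternal age and education. The text describes them only as covering confidence and stress, so the lists still need reconciling.

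**A large power gain is tempting to infer.** If pre-enrolment days had SD 8-10 and were all removed, the SE would fall from 1.79 to 1.64-1.56, and power of a t test on 4 degrees of freedom would rise from 56% to 63-67%. The document does not support this. It gives no SD for those days. The 56% assumes no covariates at all, whereas the regression already names several. The calculation also needs those days to be independent of later stay. Discharge requires a body weight above 2 kg, so an infant enrolled later may have fewer days left.

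**Adjusting for days to eligibility is tempting too.** They arise after the NICUs were randomized, under staff who cannot be fully blinded, and nurse training and unit policies act at NICU level before any one infant enrols. Adjustment could remove part of the effect. A chart-based date lessens this but does not cure it.

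**A reader might infer that early exits bias the result.** If 5-10% of one arm left 7-14 days early, the shift would be 0.05 × 7 = 0.35 to 0.10 × 14 = 1.4 days. Those rates and durations are invented and apply to one arm only. The 10% drop-out concerns families in the study and is not stated to be departure from hospital. The item "top three reasons for early discharge home" belongs to the pre-trial survey of NICUs. Nor does the document define death as a favourable short stay; it leaves the handling unstated, which is a usual matter for an analysis plan.

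**Conclusion.** The point holds in a limited form. Total stay is a valid and policy-relevant endpoint. The weakness is that part of it is settled before individual exposure, while the first-listed primary test is unadjusted and the two-level model does not name birth weight or acute severity, both available from the listed data. The mismatch between the model, the data list and the Discussion is firm and rests on no assumption.

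The gain from better adjustment is modest and uncertain: an SE of about 1.74-1.69 instead of 1.79 days if 10-20% of within-NICU variance is removed, and less beyond the covariates already named. These figures rest on SD 15, intra-cluster correlation 0.01, 264 evaluable infants per arm, two-sided 0.05 and an assumed share of variance. The document does not support a claim of bias in expectation from the admission clock, unless time to enrolment differs systematically by arm. The change is worth making because it costs almost nothing.

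**What to change.** 1. Keep total stay from admission as the primary endpoint.
2. Make the covariate-adjusted cluster analysis the primary effect estimate, and keep the t test as supporting. Prespecify a closed list of infant-level covariates that includes SNAPPE-II and birth weight (or the stated gestational age plus small for gestational age, with the Discussion reworded to match). How many NICU-level terms six NICUs can carry is a separate question.
3. Add chorioamnionitis, maternal age and maternal education to the data form, or drop them from the model.
4. Record from the chart the date on which eligibility was first met, and report days from admission to that date by arm. Use them only in a sensitivity analysis: either the adjusted model with that term, or stay from eligibility to discharge. The 90 pilot infants can show how variable these days are.
5. Optional: a sensitivity analysis of time to discharge with the discharge criteria met, treating death, transfer or earlier departure as competing events.

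Cost: wording, one chart date, up to three extra data items and a small amount of analysis. No extra infants and no change of endpoint. Because the main study is already under way, the covariate list should be fixed before outcomes are compared by arm, and any added data items should be taken retrospectively from charts for infants already enrolled.

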**Discussion:**

This study will assess the feasibility and cost-effectiveness of FICare in China. By establishing that FICare is a practical model of NICU care for stable preterm infants in China, this project will have a significant impact on health outcomes, medical practice and policy, and the cost of medical care. The approach used in this project could be transferable to many other areas of medical care, such as pediatrics, chronic care, and geriatrics. Data in this project can be used to inform health policy in NICUs across China so that parents are allowed to enter the NICU and be at their infant’s bedside during the baby’s hospitalization, and modifying the design of NICUs in China to facilitate the participation of parents in caring for their newborns.

**Trial registration:**

Chinese Clinical Trial Registry ChiCTR-TRC-14004736

## Background

Over the past decade, the percentage of neonatal intensive care unit (NICU) admissions in China accounted for by preterm infants has increased by a third from 19.7 to 26.2 % [1]. With advances in NICU medicine, more and more extremely premature infants are also being successfully rescued in China. However, although equipment and technology in Chinese NICUs has improved dramatically in recent decades, the overall model of care for NICU newborns remains unchanged. As a national policy, parents are not allowed to enter the NICU ward during the infant’s entire stay, with the care of these infants provided exclusively by medical specialists. This is in stark contrast to the regular nursery, where care is provided by the parents from birth.

The model of NICU care in China has been justified because of concerns over infection control and for convenient patient management by medical professionals. There is also a tradition of confinement of childbirth. This tradition, combined with general concerns about inadequate hygiene habits has allowed the current NICU model of care to go unchallenged, but is not based on any medical evidence. For example, the incidence of nosocomial infection in NICUs of hospitals in mainland China was reported to be 11.6 % in 2007 [2], which is similar to that of Taiwan [3] and Italy [4], but higher than that of the USA [5] and Canada [6]. Reducing nosocomial infections in neonatal intensive care is always of pivotal importance in decreasing the mortality and morbidity of critically ill neonates [7]. It is understandable that the medical care of critically ill preterm infants should be provided by medical professionals; after these infants are clinically stable, many still need to stay in the NICU for a very long time before they meet the discharge criteria. The current separation of mothers and their newborn infants during the infants’ stay in the NICU when they are stable but still require medical intervention is very unfair, on both the newborn infants and their mothers.

[name] and [name] in Mount Sinai Hospital, Toronto, Canada, [8] have recently published a pilot study of a novel model of NICU care called ‘family integrated care’ (FICare), which involves parents in the care of their NICU infants and lets them participate in the care team. The results showed that, compared with matched controls, implementing FICare resulted in a 25 % increase in weight gain, an 80 % increase in the rate of breastfeeding, a 25 % decrease in parental stress and a significant reduction in nosocomial infection and critical incident reports. The Canadian FICare study group has now started a cluster randomized controlled trial in 18 NICUs across Canada. Now the question is: If it works well in Canada, can we do anything like this for NICU infants in China? The project proposed here will take the principles of the FICare model and see how they can be applied to Chinese NICUs and what the outcomes are.

